ED psychopathology will be assessed using the Eating Disorders Examination Questionnaire (EDE-Q [32]). The EDE-Q consists of 28 items measuring the cognitions and eating disturbances associated with ED, as well as diagnostically relevant behavioral features of ED. Items can be allocated to four subscales: Restraint, Eating Concern, Shape Concern, and Weight Concern. Mean subscale scores and a mean global score are calculated in order to determine overall eating pathology [32]. The EDE-Q has high internal consistency (α ≤ 0.97) and is sensitive to change [33].Comorbid mental disorders will be assessed using the Patient Health Questionnaire (PHQ-D [34]). The PHQ-D consists of 15 items and is used to screen for symptoms of depressive disorders, panic disorder, and psychosocial functioning. The PHQ-D has excellent criterion validity and good internal consistency for depressive disorders (α = 0.88) [34].Treatment motivation will be assessed using the University of Rhode Island Change Assessment Scale—Short Version (URICA-S [35]). The URICA-S consists of 16 items, measuring four of the six stages of change (i.e., Pre-contemplation, Contemplation, Action, and Maintenance) according to the TTM [8]. Readiness for change scores will be calculated for each patient by summing the mean contemplation, action, and maintenance subscale values of the URICA-S, before subtracting the mean precontemplation subscale value [36]. The URICA-S shows acceptable to good internal consistency (α = 0.61–0.85), as well as strong criterion validity [35].Treatment uptake behaviors will be assessed using a short questionnaire developed for this study. Patients will be asked to select from a list which treatment services they have previously or currently engaged with, and to what extent (e.g., phone contact, appointment made/attended). ED treatment services are varied, including inpatient, partial inpatient, and outpatient treatment in psychiatric/psychosomatic clinics, outpatient psychotherapeutic and nutritionist services, and digital eHealth interventions. For the purposes of this study, treatment uptake will be defined as attending appointments at any of these treatment providers, however, preparatory actions such as researching treatment options and time spent on the wait list will also be assessed.Hope and confidence toward recovery will be assessed using two visual analogue scales. Patients will be asked to indicate how hopeful and confident they are regarding their own recovery. Each patient’s scores will be calculated by measuring the distance (0-100 mm) on the visual analogue scales between the anchor (no hope/confidence) and the patient’s selection, with higher scores indicating greater hopefulness and confidence toward recovery.A post-intervention questionnaire will be used to assess patients’ feedback regarding the authenticity, empathy, and likeability of the person featured in the narrative video, as well as the usefulness of the video(s) as a whole. A subgroup of six patients (determined through Research Randomizer [37]) will also be invited to participate in a semi-structured interview to provide further insights into their perception of the authenticity, empathy, likeability, and usefulness of the video(s), so as to allow for a more thorough and qualitative understanding of how these are experienced by patients.

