### Outcomes

#### Main outcome measures

Main outcome measures of this study will be changes in patients’ treatment motivation and treatment uptake behaviors. Changes in treatment motivation will be measured by comparing patients’ baseline (T0) readiness for change scores (URICA-S) to scores immediately after viewing the videos (T1), at one-week (T2) and three months follow-up (T3). Changes in treatment uptake will be measured by comparing the amount of treatment seeking activities indicated at baseline (T0), at one-week (T2) and three months follow-up (T3).

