### Strengths and limitations

A strength of this study is the strong integration of lived experience into the intervention, which has been increasingly advocated [19, 38, 39]. A further strength is the inclusion of clinically relevant outcome measures, including treatment uptake behaviors at several time points in response to engagement with patient narratives. The inclusion of such measures will allow the results of this study to more easily translate into and inform clinical practice. The long follow-up period of three months is roughly in accordance with the average wait times for psychotherapeutic treatment in Germany [40, 41], although this varies depending on region, disorder, and type of service. The study design will allow both short-term and long-term effects of this intervention to be examined. Limitations of this study include a selection bias, as the recruitment focuses on patients attending a diagnostic appointment at the Medical University Hospital Tübingen. Nevertheless, a large proportion of persons who attend such appointments fail to undertake any further actions, and therefore may benefit greatly from this intervention.

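### Treatment uptake, one of the two main outcomes, is stated as attended appointments in one section and as a change in the amount of treatment seeking in another, with no reference period shown

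*Protocol article*

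**What the plan says.** All references are to the protocol article.

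- **Status.** Main outcome measures: "Main outcome measures of this study will be changes in patients’ treatment motivation and treatment uptake behaviors". Hypotheses 2 and 4 (Study aims) concern uptake and are worded as a likelihood.
- **First statement.** Self-report measures: "treatment uptake will be defined as attending appointments at any of these treatment providers". The same sentence sets other steps apart: "preparatory actions such as researching treatment options and time spent on the wait list will also be assessed".
- **Second statement.** Main outcome measures says that change in uptake is obtained by "comparing the amount of treatment seeking activities indicated at baseline (T0), at one-week (T2) and three months follow-up (T3").
- **The item.** Patients mark on a list "which treatment services they have previously or currently engaged with, and to what extent (e.g., phone contact, appointment made/attended").
- **Who may enter.** Study participants excludes patients whose last treatment fell within four weeks of study start, and Exclusion criteria excludes those now in ED treatment. Older treatment is allowed.
- **Timing.** Procedure places T2 at one week and T3 at three months after the video. TAU patients are assessed at T0 and T3 only.
- **Analysis.** The Treatment uptake behaviors paragraph of Statistical analyses plans Pearson chi-square tests of all four groups, TAU included, at T0, T2 and T3.
- **Waiting times.** Strengths and limitations: "The long follow-up period of three months is roughly in accordance with the average wait times for psychotherapeutic treatment in Germany". The sentence goes on to say that this varies by region, disorder and service.

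**The concern.** The two statements describe different variables. One is an event: an appointment was attended or it was not. The other is a quantity, compared with baseline, drawn from what reads as a wider set of behaviors. They share a name, and the hypotheses and the analysis paragraph use that name without saying which variable is meant. The reported result for Hypotheses 2 and 4 could therefore depend on which section is followed.

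The second issue is the baseline. Main outcome measures compares T0 with T2 and T3, but the only item described covers previous and current engagement without a start date. At T0 that is treatment history. At follow-up it is either the same history carried forward or a short interval. In neither case is T0 clearly a like-for-like baseline.

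This also matters for the pilot's own purpose. Sample size says that the trial should identify a meaningful primary outcome and supply data for planning a larger one. An uptake rate whose definition and period are unsettled is a poor planning figure.

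**Working it through.** **Step 1: the plan's only figure.** 4 groups × 25 patients = 100, as Sample size states. No alpha, power, effect size or uptake rate is given, so no power calculation depends on the definition.

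**Step 2: the two statements applied to the same patient.**

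| Course of events | Attendance (Self-report measures) | Amount compared with T0 (Main outcome measures) |
|---|---|---|
| Telephones and books, nothing attended by T3 | no uptake | may rise |
| Joins a waiting list only | no uptake | may rise |
| Attends an appointment after T0 | uptake | may rise |
| Treated before study entry, does nothing after T0, history carried forward | counted as uptake | no change |

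The first two rows show the mismatch. The entries say *may rise* because Main outcome measures does not list which activities are counted. The last row is the reference-period problem.

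**Step 3: which statement fits the rest of the text.** A likelihood (Study aims) and a chi-square test (Statistical analyses) both suit a category. Neither suits a change in a count. Main outcome measures is the section out of line.

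**Step 4: the reference period.** Under the entry criteria, current treatment at T0 should be nil, so what T0 can record is past treatment.

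- *History carried forward.* Let h be the share of each arm with past attendance and p the share newly attending, taken as independent of h. The share ever attending is h + (1 − h)p. A true difference p₁ − p₂ then appears as (1 − h)(p₁ − p₂). Randomization balances h in expectation, so this dilutes the difference and does not bias it.
- *Interval answers at T2 and T3.* An open-ended history at T0 is compared with one week and three months, so a change score mixes periods of different length.

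**Step 5: attendance and waiting time (illustration only).** The document gives a wait of about three months for psychotherapy. Everything else here is assumed: all services have that wait, and all seekers start on day 0.

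- Share seen by T3: 50% if waits are symmetric about three months; 1 − exp(−1) = 63% if exponential with mean three months.
- Share seen by T2, exponential: 1 − exp(−7/91) = 7.4%.
- Suppose 30% versus 60% seek treatment. Attended by T3: 15% versus 30%, or 19% versus 38%.
- Power, two-sided 5%, n per group: Φ{[|p₁ − p₂| − 1.96·√(2p̄(1 − p̄)/n)] / √([p₁(1 − p₁) + p₂(1 − p₂)]/n)}.

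| Comparison | All seekers counted | 63% seen | 50% seen |
|---|---|---|---|
| 30% vs 60%, 25 per arm | 57% | 31% | 24% |
| 30% vs 60%, 50 vs 50 pooled | 87% | 56% | 43% |
| 30% vs 50%, 25 per arm | 30% | 17% | 14% |
| Four groups 60/50/30/30%, 25 each, chi-square on 3 df | 58% | 31% | 23% |

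The last row uses non-centrality 25·Σ(pᵢ − p̄)²/[p̄(1 − p̄)]. Expected attenders at T2 are 25 × 0.30 × 0.074 = 0.6 to 25 × 0.60 × 0.074 = 1.1 per arm.

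**Step 6: T2 and TAU.** Statistical analyses includes TAU in the T2 test. Procedure gives TAU no T2 assessment. The four-group T2 test cannot be run as described.

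**The case against.** The strongest reply is that Self-report measures gives an explicit study definition, and that the hypotheses and the test agree with it. On this view Main outcome measures is loosely worded and attendance is what is meant. Nor does that section say that its amount includes preparatory steps. This narrows the point but does not remove it: the section out of line is the one that specifies the main outcomes, and an amount of treatment seeking compared with baseline is not attendance yes/no on any reading.

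On the reference period, the article describes a questionnaire that is not reproduced, and it names previous and current engagement separately. The full instrument may keep them apart. A reader might infer that past treatment *will* be counted as uptake; the text supports only that it *could* be.

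On waiting times, a reader might infer that attendance by T3 mainly measures service capacity, that almost nobody can attend by T2, and that a null result would be uninterpretable. The document does not support this. Its figure is for psychotherapy and is said to vary, the uptake definition also covers nutritionist and eHealth services, and telephone contact, bookings and waiting-list time are collected and would help to interpret a null result. The power figures rest on assumed rates in a pilot that makes no power claim.

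It might also be inferred that the definition is open to choice after the data are seen. A full protocol or analysis plan, not shown here, may already fix it.

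**Conclusion.** The point holds as a contradiction in the text plus a smaller gap. Uptake is defined as attendance in one section and measured as a change in the amount of treatment seeking in the section on main outcomes; the hypotheses and the test fit the former. This needs no assumptions. That pre-randomization treatment could enter the follow-up count, and that T0 is not a like-for-like baseline, holds on the one item described and is subject to the full questionnaire.

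The contradiction has no single numerical size. The calculations show only that the choice can matter: on the assumed waits, moving from seeking to attendance cuts power at 25 per arm to between about two fifths and three fifths of its value. They do not show that attendance is the wrong main variable. Choosing between attendance and a broader composite is a trade-off for the sponsor: attendance is the harder endpoint, and a composite would capture patients still waiting.

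**What to change.** 1. Use one binary uptake variable in Study aims, Self-report measures, Main outcome measures and Statistical analyses. In line with the existing definition, this could be: at least one appointment attended since the T0 questionnaire, by T3.
2. Report treatment seeking steps since T0 (telephone contact, appointment made, waiting list) as a separate, named outcome, because attendance alone may miss patients still waiting at three months.
3. Word the T2 and T3 items with a reference period, such as 'since your baseline questionnaire'. Use the T0 answers as treatment history only, not as a value to subtract.
4. Present T2 descriptively for the three video arms, and remove TAU from the T2 test.

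The cost is small wording changes to a study-specific questionnaire and to the sections named. The behaviors are already being collected. If some patients have already answered the follow-up items, the change should be dated and the earlier answers identified. The definition should be fixed before outcome data are examined by group.

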
#### Interventions

The narrative videos used in this intervention were developed collaboratively in a participatory research process with a former patient with an ED, while also being based on the results of a recent systematic review of barriers and facilitators for help-seeking in patients with ED [12]. Preliminary versions of these videos will be trialed in a pre-test study with a healthy student population. The final videos will be approx. six minutes in length (+/- 1 min difference) and feature a person of the same age and gender. The former patient featured in the video is a young woman with a healthy body weight, and it is not explicitly stated which symptoms or ED diagnosis she suffered from. Instead, EDs are discussed as a whole, and the content of the videos focuses on specific aspects of the former patient’s treatment journey, including what motivated her to seek treatment and how her life has changed post-recovery. As part of the pilot study presented here, a parallel 4-arm pilot randomized controlled trial (RCT) approach will be used to evaluate the efficacy of patient narrative videos. Patients will be randomized into one of four groups for the intervention: one group (IG1) will receive access to a video featuring the personal experiences of a former patient with an ED regarding the barriers and facilitators she faced when seeking treatment, with particular focus on stigma, shame, and guilt, as well as the importance of social support. The second group (IG2) will receive access to a video featuring an ED specialist, in which the same barriers and facilitators to treatment presented by the recovered patient will be discussed, but from a professional perspective. The Control Group (CG) will receive access to a video in which the recovered patient will discuss the same barriers and facilitators to treatment, but for a somatic condition unrelated to ED (i.e., torn knee ligament). The remaining patients randomized in the Treatment-as-Usual Group (TAU) will not receive access to any videos.

### Procedure

An overview of the study plan and assessment materials are presented in Figs. 1 and 2, respectively. Following a baseline assessment (T0), patients will receive access to one of the three videos in a controlled setting at the Medical University Hospital Tübingen. After watching the videos (T1), patients will complete a series of questionnaires to assess any immediate changes in treatment motivation. A subgroup of patients will also be invited to participate in a semi-structured interview. Patients will be contacted for follow-up one week (T2) and three months (T3) after watching the videos. TAU patients will complete assessments at T0 and T3 but will not receive access to any videos.

**Fig. 1 Fig1:**
[figure not shown]
Study plan

**Fig. 2 Fig2:**
[figure not shown]
Overview of assessment materials

### Outcomes

#### Main outcome measures

Main outcome measures of this study will be changes in patients’ treatment motivation and treatment uptake behaviors. Changes in treatment motivation will be measured by comparing patients’ baseline (T0) readiness for change scores (URICA-S) to scores immediately after viewing the videos (T1), at one-week (T2) and three months follow-up (T3). Changes in treatment uptake will be measured by comparing the amount of treatment seeking activities indicated at baseline (T0), at one-week (T2) and three months follow-up (T3).

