## Study aims

The proposed study will examine the effects of patient narratives provided in video format for patients with ED. In particular, the role of patient narrative videos on patients’ treatment motivation and uptake of treatment services will be assessed. The study further aims to ascertain the feasibility and acceptability of patient narratives, as well as establishing data to identify suitable outcomes and sample size calculations for a larger trial.

Patients will be randomly assigned to view one of three narrative videos, presented from the perspective of a former and currently recovered patient with an ED (Video A), an ED specialist (Video B), and the same former patient reporting on a somatic condition unrelated to ED (Video C). It is expected that patients who receive access to narrative videos from the perspective of a former patient with an ED (Video A) or an ED specialist (Video B) will show:

stronger increases in treatment motivation (Hypothesis 1).and increased likelihood to engage in treatment uptake behaviors (Hypothesis 2).

compared to patients who receive access to a narrative video unrelated to ED (Video C) or patients who receive access to no videos.

It is further expected that patients who receive access to a narrative video from the perspective of a former patient with an ED (Video A) will show:

stronger increases in treatment motivation (Hypothesis 3).and increased likelihood to engage in treatment uptake behaviors (Hypothesis 4).

compared to patients who receive access to a narrative video from the perspective of an ED specialist (Video B).

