#### Treatment uptake behaviors

Pearson’s chi-square tests of contingencies will be used to assess the relationship between patients’ group allocation (IG1/IG2/CG/TAU) and treatment uptake behaviors at T0, T2, and T3.

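### The main uptake outcome is measured as an amount of seeking activity, which conflicts with the protocol's own attendance definition and need not rise with treatment entry

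*Protocol article*

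**What the plan says.** The protocol article describes treatment uptake, one of its two main outcomes, in four places.

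- **Main outcome measures:** change in uptake is assessed by "comparing the amount of treatment seeking activities indicated at baseline (T0), at one-week (T2) and three months follow-up (T3").
- **Self-report measures:** "treatment uptake will be defined as attending appointments at any of these treatment providers". The same sentence continues that "preparatory actions such as researching treatment options and time spent on the wait list will also be assessed". The questionnaire asks patients to select "which treatment services they have previously or currently engaged with, and to what extent (e.g., phone contact, appointment made/attended").
- **Study aims:** the hypothesis is an "increased likelihood to engage in treatment uptake behaviors (Hypothesis 2"), and Hypothesis 4 is worded in the same way.
- **Statistical analyses, Treatment uptake behaviors:** Pearson's "chi-square tests of contingencies will be used to assess the relationship between" group allocation and "treatment uptake behaviors at T0, T2, and T3".

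Under Strengths and limitations the article adds: "The long follow-up period of three months is roughly in accordance with the average wait times for psychotherapeutic treatment in Germany".

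**The concern.** Three of the four places fit a yes/no outcome: a definition by attendance, a hypothesis about likelihood and a test for categories. The outcome section is the exception, because it measures how much seeking was done.

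Seeking is a means to an end and can stop once it succeeds. A patient placed at first contact may have little to list, while a patient turned away by several services may have much. Follow-up is about as long as the average wait for psychotherapy, so a good share of patients could still be searching or waiting at T3 for reasons of service capacity.

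The Sample size section says the pilot is meant to identify a meaningful primary outcome and supply data for sizing a larger trial. An uptake measure that does not follow treatment entry serves both aims poorly.

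**Working it through.** **The plan's own figure.** The only design number is the sample size: 4 groups × 25 = 100, as stated. No power calculation stands behind it, and this point does not depend on it.

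**Check 1: two patients under each reading.** Both patients are assumed. The searcher researched options, telephoned four services, is on a wait list and attended nothing. The placed patient made one contact, had one appointment made and attended it.

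| Reading | Searcher | Placed |
|---|---|---|
| Attended, yes/no (Self-report measures) | 0 | 1 |
| Contacts + made + attended | 4 | 1 + 1 + 1 = 3 |
| The same plus preparatory items (research, wait list) | 4 + 2 = 6 | 3 |
| Number of services contacted | 4 | 1 |

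Varying the searcher's contacts from 1 to 6:

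- Without preparatory items, the searcher is behind at 1 or 2 contacts, level at 3 and ahead from 4.
- With preparatory items, the two are level at 1 contact (3 against 3) and the searcher is ahead from 2.
- On services contacted, they are level at 1 and the searcher is ahead from 2.

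If every attended session counts and the searcher has four contacts, the placed patient scores 2 plus the number of sessions. Three sessions put the placed patient ahead without preparatory items (5 against 4). With preparatory items, three sessions still leave the placed patient behind (5 against 6) and six put them ahead (8 against 6).

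**Check 2: group means.** Suppose a share *p* start searching, each contact succeeds with probability *s*, and a patient stops on success or after *m* contacts. Then

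- attended = p × [1 − (1 − s)^m]
- mean contacts = attended / s
- contacts + made + attended = mean contacts + 2 × attended, with one appointment made and one attended per success.

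The rates are assumptions; the article gives none. Control: p = 0.50, s = 0.25. Video: p = 0.65, s = 0.40.

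With m = 6:

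- Control attended: 0.50 × (1 − 0.75^6) = 0.411. Contacts: 0.411 / 0.25 = 1.64. Full count: 1.64 + 2 × 0.411 = 2.47.
- Video attended: 0.65 × (1 − 0.60^6) = 0.620. Contacts: 0.620 / 0.40 = 1.55. Full count: 1.55 + 2 × 0.620 = 2.79.
- Ratios, video to control: attendance 0.620 / 0.411 = 1.51; full count 2.79 / 2.47 = 1.13; contacts alone 1.55 / 1.64 = 0.94.

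With m = 4:

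- Attendance 0.342 to 0.566 (ratio 1.65).
- Full count 2.05 to 2.55 (ratio 1.24).
- Contacts alone 1.37 to 1.41 (ratio 1.03).

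Now hold s at 0.25 and raise only p from 0.50 to 0.65, with m = 6. Attendance goes from 0.411 to 0.534 and contacts from 1.64 to 2.14. Both ratios are 1.30, so nothing is diluted.

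**The case against.** The strongest reply is that the article already defines uptake as attendance, and under that definition the placed patient scores 1 and the searcher 0. This is correct, and it is why the point is a conflict between sections rather than a flaw in every reading.

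A reader might infer that wait-list time is one of the counted activities. The text does not support that. The outcome section lists no activities, and the self-report section sets wait-list time apart as something assessed in addition.

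A reader might also infer that an unsuccessful searcher always outscores a placed patient. That does not hold either:

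- The questionnaire is described as a list of services with the extent of engagement, so repeat calls to one service need not add up.
- Because it asks about previous as well as current engagement, a placed patient's earlier contacts stay reportable.
- If sessions are counted, the placed patient can lead.

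The fall in contacts from 1.64 to 1.55 needs two conditions. Appointments made and attended must be left out, and the video must raise success per contact, for which the article offers no evidence.

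Finally, a counting rule may stand in a fuller protocol or analysis plan, and its absence from an article is not the complaint. The disagreement between the stated definition, the stated outcome and the stated test remains in the text as published.

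**Conclusion.** The point holds in a limited form. The outcome section measures an amount of seeking, which does not agree with the attendance definition, the likelihood hypotheses or the chi-square test. Followed as written, it scores search volume rather than treatment entry.

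As a count, it can rank an unsuccessful searcher level with or above a patient placed at first contact, and it can shrink a real gain. At the assumed rates an attendance ratio of about 1.5 becomes 1.13 on the full count. The shrinkage rests on the video improving success per contact; if it only brings more patients to start searching, there is none. An actual reversal is possible but depends on the counting rule.

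A reader might go further and conclude that the pilot would discard or mis-size uptake for the larger trial. That does not follow, because attendance is recorded and could still be examined.

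**What to change.** In the section on main outcome measures, replace the amount with the definition already given under self-report measures: at least one attended appointment at a listed provider since T0, yes or no, at T2 and T3. Use the same variable in the chi-square comparison. The Procedure section has the treatment-as-usual group assessed only at T0 and T3, so the T2 comparison can include only the three video groups.

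Report separately, as descriptive or secondary outcomes, the furthest step reached (researched, contacted, appointment made or wait-listed, attended), the preparatory actions and the wait-list time. The furthest step is less suited to the main test. With a level for no step, five levels by four groups make 20 cells for 100 patients, or 5 per cell on average, and Pearson's test ignores the ordering. The yes/no outcome has 8 cells, or 12.5 per cell on average.

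The cost is small. The questionnaire already records whether an appointment was attended, so this is mainly a scoring rule, provided the follow-up form lets engagement since T0 be told apart from earlier engagement. The downside is that a yes/no outcome gives no credit for preparatory effort by patients still waiting at three months; the furthest-step measure would show it.
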